#### Secondary Outcomes

Data used to determine the usability as well as the subcategory of feasibility will be assessed through multiple methods (see Table 2). These methods help to get deeper insight and can improve the reliability and validity of the findings [40]. We will combine quantitative (ie questionnaires, task completions, and log events) and qualitative (ie, interviews and field notes) methods to produce a rich data set, which is especially recommended in health informatics research [41,42].

**Table 2 table2:** Secondary outcomes of the usability measures and logged events as well as requested information measures.

Content	Recording method
Field notes (eg, participation in tests and training)	Qualitative and quantitative analysis
Interviews on satisfaction	Qualitative analysis
Number of completed training sessions	Quantitative output of the InCoPE^a^-App
Number of successfully completed testing periods	Quantitative output of the InCoPE-App
Number of rejected exercises	Quantitative output of the InCoPE-App
Kind of rejected exercises	Quantitative output of the InCoPE-App
Mean and range of the actual duration of the tests and the training sessions	Quantitative output of the InCoPE-App
Number and content of telephone calls	Qualitative analysis
Number and content of emails	Qualitative analysis
Satisfaction with the training session	Request after training session
Participation of the participant	Request after training session

^a^InCoPE: Individualized Cognitive and Physical Exercise.

Several forms of field notes, such as participation of participants after each test and exercise session, will be documented during the whole intervention. Additionally, nursing assistants will be asked to submit feedback, and we will regularly get in touch with nursing assistants by phone calls and emails to identify possible problems that arise when delivering the individualized exercise program through the InCoPE app.

The logged events and other pertinent information (see Table 2) are a substantial part of the usability with their subgenre feasibility. These feasibility measures place focus on app contents instead of human-technology interface. The feasibility measures are used to assess practicality and satisfaction as well as acceptance of the individualized exercise program but also the respective exercises and the testing. To this end, variables aimed at the exercises, testing, and participation will be collected by analyzing logged events during the entire 18-week intervention.

Interviews will focus on satisfaction with the InCoPE-App. The open-ended approach of Georgsson and Staggers [43] will serve as reference to ask users about aspects of the InCoPE-App, ranging from good to poor usability. We will ask 3 questions: (1) What parts of the system did you think were well designed? (2) Which parts of the system did you think were inadequately designed? (3) Do you have any other comments about the system functions and regarding its usability? All interviews will be conducted on a guided basis and will be held in German. With informed consent of the participants, the interviews will be recorded using a voice recorder (Philips DVT2050, Eindhoven, Netherlands).

Additional secondary outcomes will be assessed to obtain a holistic view of the participants who will be trained with the InCoPE-App. These physical and sociodemographic variables and respective assessment tools are presented in Table 3.

**Table 3 table3:** Secondary outcomes on physical and sociodemographic information.

Dimensions	Assessments	Pre	Post	Implemented in the InCoPE^a^-App
Grip strength	Balloon manometer [44]	Yes	Yes	Yes
Frailty	Standardized phenotype of frailty in older adults [45]	Yes	No	Yes
Pain	Single item	Yes	Yes	Yes
Sociodemographic data and medical information	Singe item	Yes	No	No
Body height and weight	Single item	Yes	No	Yes
Fear of falling	FES-I^b^ [46]	Yes	No	No

^a^InCoPE: Individualized Cognitive and Physical Exercise.

^b^FES-I: Falls Efficacy Scale International Version.

Grip strength is measured with a balloon manometer [44]. Participants sit on a chair without armrests and solid feet-to-floor contact. Participants will be instructed and verbally encouraged to squeeze the balloon as hard as possible. Both hands will be tested. While being tested, participants should keep the upper arm in contact with the trunk and flex the elbow 90°. Additionally, the wrist is held in a neutral position (thumb up). To examine frailty, the Fried Frailty Criteria will be used [45]. Body weight, self-reported exhaustion, grip strength, walking speed, and level of physical activity in the past 3 months will be assessed before and after the intervention.

Nursing assistants will ask the participants for their body height and weight and enter them directly into the InCoPE-App. Fear of falling will be measured with the German version of the Falls Efficacy Scale International Version (FES-I). The questionnaire consists of 16 items rated on a 4-point scale that are combined into a total score. High values indicate a high fear of falling. Several studies have reported this instrument’s high reliability and validity [46].

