### Participants

To evaluate the InCoPE-App in terms of usability and effectiveness, 2 different study samples are required (see Figure 1). The first sample will include the future users of the InCoPE-App (ie, nursing assistants). To this end, initial contact will be established through the heads of care facilities in southwestern Germany who suggest potentially interested nursing assistants, who will subsequently receive detailed information about the aims and the content of the study. The following inclusion criteria must be fulfilled: (1) willingness to participate in the training to familiarize themselves with the InCoPE app, (2) command of the German language as the InCoPE-App is only available in German at this time, and (3) employment at the nursing home for at least 18 weeks. External employees (eg, physical therapists) will be excluded.

The second sample will include participants with primary dementia living in nursing homes. This sample will be drawn to evaluate usability and trends toward the effectiveness of the individualized exercise program as delivered by the InCoPE app. Participants in the second sample will be selected by nursing assistants. Before entering the study, written consent by participants or their legal guardians will be obtained. Prior to the intervention, a clearance certificate from the participant’s general practitioner will be collected, which will also include information about the dementia diagnosis and other pertinent information such as medication intake and comorbidities. Additional inclusion criteria are (1) Alzheimer disease, vascular dementia, or other primary dementia; (2) mild to moderate stage of dementia (Mini-Mental State Examination [MMSE]: 10-24); (3) age older than 65 years; and (4) walking ability of at least 10 meters with or without a walking aid. Exclusion criteria include (1) secondary dementia, (2) other severe cognitive impairments, (3) other severe neurological conditions, (4) other severe acute diseases, and (5) severe motor impairments.

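### Height and weight are obtained by asking residents with dementia, so these secondary variables, and by inference the weight component of frailty, rest on recall

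*Protocol article*

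**What the plan says.** All of this is in the Methods of the Protocol article.

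- **Source of height and weight (Secondary Outcomes, text after Table 3):** "Nursing assistants will ask the participants for their body height and weight and enter them directly into the InCoPE-App".
- **Who is asked (Participants):** residents must have "mild to moderate stage of dementia (Mini-Mental State Examination [MMSE]: 10-24".
- **Frailty (Secondary Outcomes, text after Table 3):** the Fried criteria are named, and the next sentence lists the components, with assessment at both time points: "Body weight, self-reported exhaustion, grip strength, walking speed, and level of physical activity in the past 3 months will be assessed before and after".
- **Table 3:** the row "Body height and weight" is described as a single item, collected at the pre assessment only and implemented in the app. Frailty has its own row, also pre only.
- **General practitioner's certificate (Participants):** it covers "information about the dementia diagnosis and other pertinent information such as medication intake and comorbidities". Height and weight are not named.
- **Data checks (Statistical Methods):** plausibility is checked before analysis, with range and distribution as the examples.

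**The concern.** The article fixes a collection rule, and the rule is weak for this population. A person with mild to moderate dementia may give a weight that was true years ago, or a guess, and the assistant is told to enter the answer directly. Error of this kind plausibly depends on cognition, so it need not be purely random.

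What is at stake is the validity of two listed secondary variables and, if the same weight is used there, of one of the five frailty components. A description of how heavy or how frail the sample is would then partly reflect memory. The point concerns a stated method, so it is not a matter of detail that a condensed article leaves to a fuller document. The neighbouring description of grip strength goes down to elbow angle and wrist position.

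**Working it through.** No arithmetic applies: the article gives no figure on this point. The check is to read the relevant places side by side.

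1. **Who the participants are in this sentence.** The article uses the word for both samples; under Sample Size it means the nursing assistants. In the height-and-weight sentence the assistants do the asking, so the people asked are the residents.
2. **Their cognitive status.** An MMSE of 10-24 is an inclusion criterion, so it applies to every resident. The planned number is 44 (22 + 22). That counts who is asked, not how many would answer wrongly.
3. **Other sources of weight.** None is given. No scale, care record or proxy is mentioned for height or weight. The Table 3 entry as a single item fits a question better than a measurement. The general practitioner's certificate is a possible channel but does not name weight.
4. **Link to frailty.** Body weight comes first of the five components listed after the Fried criteria. That the asked weight is the one used there is an inference: the asking sentence stands in a separate paragraph that does not mention frailty, and Table 3 keeps the two in separate rows. The inference is reasonable because asking is the only way of obtaining weight that the article describes.
5. **Would the planned check catch an error?** A check on range and distribution finds impossible or extreme values. A believable weight that is out of date lies inside the range and passes.
6. **What depends on weight.**
   - Primary outcomes (Table 1): neither weight nor frailty is listed.
   - Sample Size: neither enters.
   - Intervention: the four exercise clusters are assigned from motor and cognitive tests, not from weight.
   - Statistical Methods: height, weight and frailty are not named, either in the baseline comparison (physical and cognitive performance) or among the subgroup variables (physical or cognitive performance, gender, fear of falling, logged events).
7. **Timing.** The text has body weight and the other frailty components assessed before and after the intervention. Table 3 gives post as no for both frailty and height and weight. The two disagree.

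**The case against.** The strongest reply is that nothing important turns on this. Table 3 variables are introduced to give a rounded picture of the participants, and step 6 above finds no planned analysis that names weight or frailty. That stands, and it limits the size of the point. It does not make the collection rule sound.

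A reader might infer more, and four such readings are not supported:

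- **That a comparison of arms on frailty is diluted.** Statistical Methods does not name such a comparison.
- **That a change between two recalled weights will be analysed and is uninterpretable.** Table 3 shows no post assessment of weight or frailty. Only the one sentence on the frailty components says otherwise, so what the documents establish here is a contradiction in timing.
- **That physical activity over the past 3 months is also recalled by the resident, making two of five components affected.** The article does not say who supplies it, and attaches self-report only to exhaustion.
- **That a recall error of a few kilograms would switch the frailty component.** The article gives no weight-loss rule, no cut-off and no recall-error figure, so no such threshold can be derived from it.

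It is also fair to object that a better source is not certain to be at hand. The discussion of strengths says that regular clinical documentation is required in nursing homes, but nowhere does the article say that it contains dated weights. Measurement at the home does not depend on such records, though it needs equipment that the article does not describe.

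**Conclusion.** The point holds as a limited data-quality defect. The article prescribes asking people with an MMSE of 10-24 for their height and weight, gives no other source, and plans a check that would miss a plausible wrong answer. The affected items are height, weight and, by inference, one of five frailty components, for all 44 planned residents. The number who would be misclassified cannot be estimated from the documents.

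No primary outcome, sample-size figure or exercise-cluster assignment is touched, so the main effectiveness and usability results are not in question. The conclusion rests on two readings: that the participants in the sentence are the residents, which the wording makes clear, and that the frailty weight is the asked weight, which is inferred. If the frailty weight comes from elsewhere, the point narrows to height and weight alone. The timing contradiction between the text and Table 3 stands independently of both.

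**What to change.** Replace the sentence so that height and weight are measured at the home, or taken from a dated care record where one exists, and are not asked of the resident. Record the source and, for a record, its date. State that the same weight is used for the frailty criteria. Change the app prompt to match.

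Reconcile the text on frailty components (before and after) with Table 3 (pre only for frailty and for height and weight), so that one schedule is stated.

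The cost is one protocol sentence, one app prompt and a few minutes per resident. The downside is that recorded values may be some weeks old. Enrollment began in October 2021, so for residents already assessed the asked value could be replaced from a dated record if the home holds one, and otherwise flagged as self-reported.

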### Sample Size

The sample size for the number of nursing assistants who will evaluate the InCoPE-App with regard to usability was defined using a probabilistic model of problem discovery for formative user research [34]. We defined a sample size comprising 22 participants to have a 90% chance of observing with a probability of 0.1. In the second study phase, outcomes also include usability in addition to the effectiveness of the InCoPE-App with respect to adaptations in physical and cognitive performance in people with dementia. For this reason, each participant will recruit 2 appropriate residents with dementia in accordance with our inclusion and exclusion criteria. We anticipate that our calculated sample size (N=44: intervention group [IG], n=22; control group [CG], n=22) will be appropriate to examine potential trends toward effectiveness of the InCoPE-App.

This sample size allows detection of moderate effects calculated using an ANOVA with repeated measures for within and between interactions. The calculation of the sample size with G*Power version 3.1.9.2 (Heinrich Heine University of Dusseldorf, Germany [47]; effect size ηp² = 0.07, α error probability .05, power 0.95) resulted in 44 participants.

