**Methods:**

We will evaluate the usability and effectiveness of the InCoPE-App by applying a mixed method design. Nursing assistants will use the InCoPE-App for 18 weeks to assess the cognitive function and physical performance of 44 people with dementia every 3 weeks and apply the individualized exercise program. We will record overall usability using questionnaires (eg, Post-Study System Usability and ISONORM 9241/10), log events, and interviews. Perceived hedonic and pragmatic quality will be assessed using the AttrakDiff questionnaire. Effectiveness will be evaluated by considering changes in quality of life as well as cognitive function and physical performance between before and after the program.

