## Methods

### Study Design

This study combines the evaluation of the usability of the InCoPE-App with the effectiveness of the individualized exercise program concerning cognitive function, physical performance, and quality of life. Thus, a mixed methods design with different methodological components will be used. The evaluation of the usability and effectiveness of the InCoPE-App will be based on the use of the app for a duration of 18 weeks in a nursing home setting. This approach represents a field study and will be carried out as a cluster-randomized controlled trial in which the InCope-App will be used with people with dementia and the individualized, multidomain exercise program will be delivered by nursing assistants with the help of the app. The nursing homes will be cluster randomized, and each nursing assistant will subsequently recruit at least 2 people with dementia (see Figure 1).

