Each nursing assistant will use the app to deliver the individualized exercise program within the 18-week intervention to 2 people with dementia. The overall usability will be assessed after the intervention using the Post-Study System Usability Questionnaire (PSSUQ) [24]. The PSSUQ gives insight into user satisfaction with a system (eg, system usefulness, information quality, and interface quality). This questionnaire can be considered a useful tool for field studies [24]. We will use PSSUQ version 3, which is comprised of 19 items such as system usefulness, information quality, and interface quality rated on a 7-point Likert scale (1: strongly agree to 7: strongly disagree) [24,34]. Furthermore, usability will be assessed using the ISONORM questionnaire [25], which covers the implementation of the 7 defined criteria based on the International Ergonomics Standard DIN EN ISO 9241-110. This questionnaire operationalizes the 7 criteria of the EN ISO 9241-10 and was developed to evaluate software development [35]. The completion of the questionnaire takes 10 minutes, and bipolar statements from 35 items are assessed using a 7-point Likert scale (1: very negative to 7: very positive) [35]. The perceived hedonic and pragmatic quality of the InCoPE-App will be assessed using the AttrakDiff 2 questionnaire [26]. This questionnaire evaluates the participants’ perceptions of the InCoPE-App by means of semantic differentials.

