### Randomization and Concealment

The residents with dementia recruited by nursing assistants will be allocated to either the CG or IG. This allocation will be performed by cluster randomization as it is not possible to blind participants, nursing assistants, or study personnel regarding group allocation. Participants in the CG will only receive conventional treatment such as individualized medication, standard care, or therapeutic applications for 18 weeks. Participants in the IG will receive the individualized exercise program in addition to conventional treatment. To ensure equal conventional treatment for the IG and CG during the intervention, it will be continuously documented.

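### The 90% problem-discovery figure assumes 22 app users, but the 22/22 resident split leaves at most about 11 assistants delivering the program, so for program delivery it is at most about 69%

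*Protocol article*

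**What the plan says.** The Sample Size section bases the usability sample on app evaluators: "The sample size for the number of nursing assistants who will evaluate the InCoPE-App with regard to usability was defined using a probabilistic model". The model is one for discovering usability problems. The section then gives the figure: "We defined a sample size comprising 22 participants to have a 90% chance of observing with a probability of 0.1". The thing observed is not named in that sentence. From the model cited, it is a usability problem.

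The same section links assistants to residents, "each participant will recruit 2 appropriate residents with dementia in accordance with our inclusion and exclusion criteria", and divides the residents as "N=44: intervention group [IG], n=22; control group [CG], n=22".

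The Study Design section sets the unit of allocation: "The nursing homes will be cluster randomized, and each nursing assistant will subsequently recruit at least 2 people with dementia". Under Randomization and Concealment, the control condition is: "Participants in the CG will only receive conventional treatment such as individualized medication, standard care, or therapeutic applications for 18 weeks".

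Two other places describe who delivers the program. Primary Outcomes says: "Each nursing assistant will use the app to deliver the individualized exercise program within the 18-week intervention to 2 people with dementia". The Abstract (Methods) describes what nursing assistants do with the app over the 18-week period: "assess the cognitive function and physical performance of 44 people with dementia every 3 weeks and apply the individualized exercise program".

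Table 1 lists the three usability questionnaires (PSSUQ, ISONORM, AttrakDiff 2) as post-intervention only.

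**The concern.** Twenty-two assistants with two residents each make 44 residents. If all 22 deliver the program to both of their residents, all 44 residents are trained and no controls remain. If 22 residents are controls in control homes, the assistants in those homes do not deliver the program. The Abstract and Primary Outcomes describe the first situation. Study Design, the allocation in Sample Size, and Randomization and Concealment describe the second.

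Usability is one of the two aims of the study, and the discovery calculation is the only justification given for the number of assistants. If about half of them never deliver the program, a reader would credit the study with a chance of finding delivery problems that its allocation does not give. It would also be unclear whose ratings enter the usability analysis. Pooling people who delivered the program for 18 weeks with people who did not would blur what the scores mean.

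**Working it through.** **Inputs, all from the protocol article**

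- Assistants sized for usability: 22; target chance 90%; problem probability p = 0.1 (Sample Size).
- Residents per assistant: 2 (Sample Size, Primary Outcomes); at least 2 (Study Design).
- Residents: 22 intervention, 22 control (Sample Size).
- Randomized unit: the nursing home (Study Design).
- Control group: conventional treatment only (Randomization and Concealment).

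**Step 1. Reproduce the stated figure.** If n users each meet a problem independently with probability p, the chance that at least one meets it is 1 − (1 − p)^n.

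- Required n for 90% at p = 0.1: ln(0.1)/ln(0.9) = 21.85, rounded up to 22.
- At n = 22: 1 − 0.9^22 = 0.9015.

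The stated 90% is therefore correct for 22 users. The calculation itself contains no error.

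**Step 2. Count the assistants who deliver the program.** Homes are randomized, so an assistant's residents share one arm. With 22 intervention residents and 2 per assistant, 22 / 2 = 11 assistants. Because Study Design allows more than 2 residents each, 11 is an upper bound.

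**Step 3. Apply the same model to 11 users.**

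- 1 − 0.9^11 = 1 − 0.314 = 0.686, about 69%.
- The chance of missing a problem with p = 0.1 is 0.9^22 = 0.10 with 22 users and 0.9^11 = 0.31 with 11.
- The smallest p found with 90% chance by 11 users: 1 − 0.1^(1/11) = 0.189, about 0.19.

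**Step 4. Check whether the other statements can be met.** For 22 assistants to deliver the program to 2 residents each, the intervention group needs 22 × 2 = 44 residents, or 88 in total at 1:1. The article has 44 in total.

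| Function of the app | Possible users | Chance of observing a problem with p = 0.1 |
|---|---|---|
| Program delivery | at most about 11 | at most about 69% |
| Testing module, if control assistants use it | up to 22 | up to about 90% |
| Testing module, if they do not | at most about 11 | at most about 69% |

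**The case against.** The strongest reply is that control assistants may be app users too. Tables 1 and 3 mark most pre and post assessments (among them MMSE, digit span, the mobility, chair stand and balance tests, and grip strength) as implemented in the app. Control residents need those assessments, and the article describes nursing assistants running the timed tests with it. This stands as a limit on scope. A reader might infer that 69% applies to the whole app, but the documents do not support that, because up to 22 people might use the testing module. Nor do they establish the opposite, since the text does not say who tests the control group. Delivery problems are unaffected either way.

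Other replies:

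- *The number 11 is inferred.* True. No section gives assistants per arm, and Figure 1 (participant flow) is not shown. A reader might take exactly 11 as the planned count, but it is only a ceiling from the stated allocation. Whatever the figure shows, 44 trained residents cannot coexist with 22 untrained controls among 44.
- *One intervention and one control resident per assistant would keep 22 users.* This conflicts with randomizing homes and with delivery to two residents each.
- *The wording about a second study phase could mean that 22 were sized for an earlier phase.* No such phase is described, and the questionnaires follow the 18-week intervention. This reading is weak.
- *Control homes could rate the app later.* The Dissemination section permits participating homes to go on using the app after evaluation. That is not a planned deployment with usability ratings, so it does not restore the 22.
- *Problem discovery is a planning heuristic, and no between-arm usability test is planned.* True, and this limits the consequence. The 90% is still stated as a property of the design.

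**Conclusion.** The point holds as an internal inconsistency with a calculable consequence. The Abstract and Primary Outcomes cannot be true together with Study Design, the 22/22 split in Sample Size, and the control condition in Randomization and Concealment.

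On the stated allocation, the advertised 90% is at most about 69% for program delivery, and the chance of missing a delivery problem with p = 0.1 rises from about 10% to at least about 31%. For the testing module the 90% is neither confirmed nor refuted.

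This rests on four assumptions: 22 intervention residents, at least two residents per assistant, both in the same arm because homes are randomized, and the independent-user model that reproduces the article's own figure. The article makes no precision claim for mean usability scores, so the conclusion does not extend to those.

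**What to change.** 1. Reconcile the Abstract (Methods), Primary Outcomes, Sample Size, and Randomization and Concealment on which assistants deliver the program and to how many residents.
2. State how many assistants use the app in each arm and for which functions, including who runs the pre and post tests in control homes.
3. Restrict the PSSUQ, ISONORM, AttrakDiff and interview analysis of the full app to intervention-group assistants who delivered the program. Report separately any ratings from control assistants who used only the testing module.
4. Restate the discovery figure for program delivery: at most about 69% at p = 0.1 or, equivalently for 11 users, 90% for problems with p of about 0.19 or more. If control assistants do use the testing module, a separate figure of up to about 90% can be given for that part.

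The cost is wording and a less favourable stated figure. Allocation, recruitment and treatment do not change.
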